### Covariates

Standardised questionnaires will be administered with a face-to-face interview by trained interviewers. Data collected will include socio-demographic (living arrangement, marital status, education, lifetime occupation), smoking, alcohol consumption, medical history, use of medications (prescribed and non-prescribed), hearing and visual impairment, falls, fear of falling (assessed with the Fall Efficacy Scale-International, FES-I) [46], cognitive function (assessed using the Montreal Cognitive Assessment, MoCA) [47], depressive symptoms (Geriatric Depression Scale, GDS) [48], anthropometric measures (height, weight, body composition (Tanita Scale BC 545N), circumference of the waist, hip, calf and mid arm), and blood pressure (Omron HEM7130).

### Participant time

Figure 1 below depicts the recruitment process and assessment schedule. Table 1 shows the detailed follow-up assessments.

**Fig. 1 Fig1:**
[figure not shown]
Study flowchart

**Table 1 Tab1:** Assessment schedule

Time point	Study period							
	Enrolment	Allocation	Post-allocation					Close-out
	*t*_0_ (baseline)	0	*t*_intv_	*t*_1_ (0 m)	*t*_2_ (6 m)	*t*_3_ (12 m)	*t*_4_ (24 m)	*t*_x_
Enrolment								
Eligibility screen	X							
Informed consent	X							
Random allocation		X						
Interventions								
Senior chef			X					
SAYGO			X					
SC & SAYGO			X					
Social			X					
Assessments								
Socio-demographic	X							
Hearing and visual	X						X	
Smoking and alcohol	X						X	
Medical history	X					X	X	
Medications	X					X	X	
Cognitive function	X				X	X	X	
Depressive symptoms	X			X	X	X	X	
Anthropometric measures & blood pressure	X			X	X	X	X	
Outcome measures								
Weight	X			X	X	X	X	
Grip strength	X			X	X	X	X	
SPPB	X			X	X	X	X	
Falls	X			X	X	X	X	
NEALD	X			X	X	X	X	
SF-12	X			X	X	X	X	
INTAKE24	X			X	X	X	X	
CHAMPS	X			X	X	X	X	
Dissemination								
Back to participants, GPs, local health professionals								X
Academic community								X

*CHAMPS* Community Healthy Activities Model Program for Seniors, *GP* general practitioners, *NEADL* Nottingham Extended Activity of Daily Living, *SPPB* Short Physical Performance Battery

### Sample size

The sample size and power calculations are based on the primary outcome of frailty score. A sample of 504 (126 in each of group) will provide 90% power at a 5% significance level (two sided) to detect a 25% reduction in the mean number of frailty criteria (reduction of 0.43 from 1.68 to 1.25) [49]. With an attrition rate of 20%, the study will enrol 600 eligible older people. This sample size will also provide 80% power at a 5% significance (two sided) to detect a 30% reduction in the rate of falls, reduction of 30% [50] in falls (from 58 to 41% [51]).

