## Methods

This trial aims to determine the effectiveness and cost-effectiveness of the SC and/or SAYGO programmes to prevent frailty in pre-frail older adults.

Design: A multi-centre randomised controlled, assessor-blinded, 2 × 2 factorial study.

Setting and characteristics of participants: Community-dwelling older adults aged 75+ (60 + Māori and Pasifika) across four sites in both the main islands of New Zealand (North and South Islands), with no upper age limit. Māori are the indigenous Polynesian people of New Zealand and Pasifika people are migrants from the South Pacific Region who are living in New Zealand. Health inequalities between the Māori/Pasifika and non-Māori/non-Pasifika are evident [26] and Māori/Pasifika people have lower life expectancy than non-Māori/Pasifika [27], so that applying uniform eligibility criteria would exclude Māori and Pasifika older people.

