### Data collection, management, and analysis

Data will be collected with face-to-face interviews and physical assessments using a standardised questionnaire completed by trained research assessors blinded to the group status of the participant in the participant’s home or local clinic. Data will be entered directly to the EDC system. Assessors are trained over a 2-day training period for all measures including standardisation. Assessors will meet regularly to support each other and observe each other’s procedures. Research-trained assessors blinded to group status will complete covariate and outcome assessments at baseline, end of the intervention (0 month  post-intervention), 6 months, 12 months and 24 months post-intervention.

Data entered in the EDC will be verified for completeness by the data quality assurance research team (see “Monitoring” section). Data from the EDC will be transferred to a statistical package (SAS and SPSS) for analysis. INTAKE 24 data are automatically linked to NZ FOODfiles and macro- and micronutrients are calculated.

The primary approach for analysis of primary and secondary outcomes will follow the intention-to-treat principle, for all participants who have at least one baseline measurement. All randomised participants will be analysed in the group they were allocated to, even if they do not attend the allocated intervention programme, are lost to follow-up, or die thereby preserving the intention-to-treat framework. The primary approach for analyses will be supplemented by a secondary analysis which will be a per-protocol analysis of outcomes for those who participated in the interventions and includes only observed cases (i.e. participants with measurements at baseline to the 24 months).

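### Enrolling 600 with 20% attrition leaves 480 participants, not the 504 on which the stated 90% power is based; the effect on power is small

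*Protocol article*

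**What the plan says.** All the relevant figures stand together in the Sample size section of the protocol article.

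- Primary outcome: "A sample of 504 (126 in each of group) will provide 90% power at a 5% significance level (two sided").
- Effect to be detected: a "25% reduction in the mean number of frailty criteria (reduction of 0.43 from 1.68 to 1.25").
- Enrolment: "With an attrition rate of 20%, the study will enrol 600 eligible older people".
- Falls: a further statement claims 80% power to "detect a 30% reduction in the rate of falls, reduction of 30% [50] in falls (from 58 to 41% [51"]). It points back to a sample size without saying whether 504 or 600 is meant.

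The section gives no standard deviation, no second attrition rate and no rounding rule. It does not say that 504 already contains an allowance for loss, and it does not say which contrast between the four groups is powered.

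Three other places bear on the size of the problem. The Methods section describes "A multi-centre randomised controlled, assessor-blinded, 2 × 2 factorial study". The section on data collection, management and analysis says that the main analysis "will follow the intention-to-treat principle, for all participants who have at least one baseline measurement". The Primary analysis method section specifies a repeated-measures model comparing the randomised groups.

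**The concern.** The text moves directly from the number needed for 90% power (504) to the number to be enrolled (600), with a 20% loss in between. Read in the ordinary way, the second number should shrink to the first when 20% is removed, and it does not. The enrolment target, the attrition allowance and the analysable number cannot all be right.

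The stated power of the primary outcome is at stake. Readers will judge recruitment and retention against these figures. A trial that enrols exactly 600 and loses exactly 20% will have met its plan and still fall short of the number on which the plan says its power rests.

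**Working it through.** **Inputs, all from the Sample size section:** 504 in total, 126 per group in four groups; 90% power; two-sided 5%; difference 0.43 (1.68 to 1.25); attrition 20%; enrolment 600.

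**1. The plan's own figure.** The number to enrol is N / (1 − attrition).

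- 504 / (1 − 0.20) = 630. The stated 600 is not reproduced; it is 30 too low.
- Rounding up within groups: 126 / 0.80 = 157.5, so 158 per group, or 632.

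**2. The reverse check.**

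- 600 × (1 − 0.20) = 480, or 120 per group.
- Shortfall: 504 − 480 = 24, or 6 per group; 24/504 = 4.8%.
- Attrition at which 600 would leave 504: 1 − 504/600 = 16%.

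**3. What the shortfall does to power.** The standard deviation (SD) is not stated. As an assumption, I solved for it from the stated inputs, taking a comparison of two groups of 126:

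- SD = 0.43 / [(1.960 + 1.2816) × √(2/126)] = 0.43 / (3.2416 × 0.1260) ≈ 1.053.
- Power at 120 per group = Φ(0.43 / [1.053 × √(2/120)] − 1.960) = Φ(3.163 − 1.960) = Φ(1.203) ≈ 88.6%.
- Difference detectable with 90% power at 120 per group = 3.2416 × 1.053 × √(2/120) ≈ 0.44, which is 0.44/1.68 ≈ 26% of the reference mean instead of 25%.

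Because the SD is an assumption, here is the range around it:

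| SD assumed | Power, 126 per group | Power, 120 per group |
|---|---|---|
| 1.00 | 92.7% | 91.5% |
| 1.05 (implied) | 90.0% | 88.6% |
| 1.10 | 87.3% | 85.7% |

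The loss from 126 to 120 per group is between 1.2 and 1.6 points across this range.

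**4. If the contrast is a factorial main effect.** Each programme would be compared across half the sample: 252 v 252 at 504, or 240 v 240 at 480. With the same difference, an SD of 1.053 and no interaction, power is 99.6% and 99.4%.

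**5. Falls, 58% v 41%.** For a two-group comparison of proportions at two-sided 5%, power is 75.3% at 120 per group, 77.3% at 126 and 84.1% at 150. About 135 per group gives 80%.

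**The case against.** The arithmetic is hard to dispute, and the strongest opposing case concerns what follows from it.

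*480 is a count of completers, not of people analysed.* The plan analyses everyone randomised who has a baseline measurement, in a repeated-measures model, and the assessment schedule has four follow-up visits. Someone lost before 24 months can still contribute earlier visits. This stands: 88.6% is a completer-only figure, and the real loss is probably smaller. It does not rescue the sentence, because the section chose to inflate for attrition and the inflation does not work out. The supplementary per-protocol analysis, restricted to participants measured from baseline to 24 months, gets no such relief.

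*The design is factorial.* If the powered contrast is a main effect, the shortfall hardly matters. This also stands as a possibility. The section gives its number per group and names no contrast, so the pairwise reading is an assumption.

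*The SD is solved backwards.* True. It is not the sponsor's planning value and should not be written into the protocol as if it were.

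*Might 600 come from multiplying by 1.2?* 504 × 1.2 = 604.8, which is close to 600, so that slip is plausible. It is only a guess about cause, and the finding does not need it.

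A reader might also infer that the falls power rests on the same number and falls with it. The documents do not support that. The falls sentence follows the figure of 600, so its reference is ambiguous, and the stated 80% does not come out at 126 per group in a pairwise comparison of proportions. The planned falls analysis is a negative binomial model of rates, for which these proportions are only a rough guide. What can be said is that the sample size behind the falls statement is unclear.

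**Conclusion.** The inconsistency is real: 600 enrolled at the stated 20% attrition gives 480, not 504, and 504 would need 630. This rests only on the article's own figures.

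Its consequence is minor. For a pairwise comparison of completers with an SD of about 1.05, power falls by 1.4 points, from 90% to about 88.6%. All three conditions are assumptions, and relaxing the completer-only or the pairwise condition makes the loss smaller. A reader might conclude that the trial is materially underpowered or should recruit more people. The figures do not support that: the estimand, the analysis and the interpretation are unchanged. This is a wrong number in a sentence others will rely on, and it should be corrected as such.

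**What to change.** Keep enrolment at 600 and correct the statement in the Sample size section, along these lines:

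> With 600 enrolled and 20% attrition, 480 participants (120 per group) are expected to complete follow-up. This gives [recomputed]% power at a two-sided 5% level for a reduction of 0.43 in [named contrast], assuming a standard deviation of [planning value].

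The sponsor should fill in its own planning SD and say whether the contrast is between two groups or is a factorial main effect. If the SD is about 1.05 and the contrast pairwise, the figure will be about 88 to 89%.

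In the falls statement, name the number of participants on which the 80% rests.

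Changing the attrition allowance to 16% is not a good alternative. It would make the sum close, but it alters a planning assumption after the fact, and nothing in the article suggests that 16% is the expected loss.

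The cost is a sentence or two of text and, on the pairwise reading, a slightly less favourable power figure. No participants are added and recruitment, which began in April 2016, is not affected.

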### Allocation

The randomisation sequence will be prepared by an independent statistician using computer-generated block randomisation and uploaded to the Electronic Data Capture (EDC) system by an administrator of the EDC. The randomisation sequence was stratified by study sites (Whangarei, Howick-Auckland, Tauranga, Invercargill) and ethnic groups (Māori/Pasifika and non-Māori/Pasifika). The allocation sequence will be concealed to all study investigators and the study coordinators involved in enrolment. Local study coordinators will assign the intervention group through the EDC after the assessors complete baseline assessments. Once randomisation has occurred, the study coordinators and participants are not blinded to group allocation. The study coordinators systematically remind all participants not to disclose the group allocation to the assessors prior to the follow-up appointments.

### Blinding

The trained research assessors will collect all baseline measurements of primary and secondary outcomes prior to randomisation. The same assessors blinded to the group allocation will conduct follow-up assessments. Assessors will be asked of their ‘blinding’ status at every assessment time point.

Fall calendars will be completed by the participants and sent to the central study coordinating office based at the University of Auckland. A blinded assessor will interview participants on the phone about the falls that are reported or to check missing data or missed submission of calendars.

All investigators will be blinded to the treatment allocation to minimise any potential influence on the progress and outcome measures except for one appointed investigator who will work closely with the site coordinators and will not be blinded to the group allocation.

### Data collection, management, and analysis

Data will be collected with face-to-face interviews and physical assessments using a standardised questionnaire completed by trained research assessors blinded to the group status of the participant in the participant’s home or local clinic. Data will be entered directly to the EDC system. Assessors are trained over a 2-day training period for all measures including standardisation. Assessors will meet regularly to support each other and observe each other’s procedures. Research-trained assessors blinded to group status will complete covariate and outcome assessments at baseline, end of the intervention (0 month  post-intervention), 6 months, 12 months and 24 months post-intervention.

Data entered in the EDC will be verified for completeness by the data quality assurance research team (see “Monitoring” section). Data from the EDC will be transferred to a statistical package (SAS and SPSS) for analysis. INTAKE 24 data are automatically linked to NZ FOODfiles and macro- and micronutrients are calculated.

The primary approach for analysis of primary and secondary outcomes will follow the intention-to-treat principle, for all participants who have at least one baseline measurement. All randomised participants will be analysed in the group they were allocated to, even if they do not attend the allocated intervention programme, are lost to follow-up, or die thereby preserving the intention-to-treat framework. The primary approach for analyses will be supplemented by a secondary analysis which will be a per-protocol analysis of outcomes for those who participated in the interventions and includes only observed cases (i.e. participants with measurements at baseline to the 24 months).

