**Methods:**

A multi-centre randomised controlled assessor-blinded study. The four intervention groups are SC, an 8-week nutrition education and cooking class; SAYGO, a 10-week strength and balance exercise class; SC plus SAYGO, and a social group (Control). Community-dwelling adults aged 75+ (60 + Māori and Pasifika) in New Zealand are recruited through health providers. Participants are not terminally ill or with advanced dementia, and have a score of 1 or 2 on the FRAIL questionnaire. Baseline assessments are completed using standardised questionnaires prior to randomisation. Four follow-up assessments are completed: immediately after intervention, 6, 12 and 24 months post-intervention. The primary outcome is frailty score, secondary outcomes are falls, physical function, quality of life, food intake, physical activity, and sustainability of the strategy. Study outcomes will be analysed using intention-to-treat approach. Cost analyses will be completed to determine if interventions are cost effective relative to the control group.

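### The supplementary per-protocol set also requires measurement to 24 months, so it selects on survival and retention as well as on receipt of the 8- to 10-week programmes (minor)

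*Protocol article*

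**What the plan says.** All of this is in the protocol article; no separate SAP is at hand.

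- **Primary set.** Under Data collection, management, and analysis: "All randomised participants will be analysed in the group they were allocated to". This expressly covers non-attenders, those lost to follow-up and those who die.
- **Status of the per-protocol analysis.** "The primary approach for analyses will be supplemented by a secondary analysis", described as "a per-protocol analysis of outcomes for those who participated in the interventions". No attendance threshold is given.
- **Second condition.** The same sentence says that this analysis "includes only observed cases (i.e. participants with measurements at baseline to the 24 months".
- **Timing.** The Interventions section gives 8 weeks for Senior Chef and 10 weeks for SAYGO and for the social group. The Abstract says: "Four follow-up assessments are completed: immediately after intervention, 6, 12 and 24 months post-intervention".
- **Attrition.** Under Sample size: "With an attrition rate of 20%, the study will enrol 600 eligible older people".
- **Models.** A repeated-measures generalised linear model is planned for the frailty score and GEE for other repeated outcomes. Falls are to be reported as a rate per person-year and as time to first fall.

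**The concern.** A per-protocol set is meant to describe people who received what they were allocated. Here that takes at most 10 weeks. Being measured 24 months after the intervention ended is a different matter: it reflects survival, health and willingness to continue. Someone who attended every session and died at month 18 leaves the set, and the 0-, 6- and 12-month measurements go too.

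The Background section says that frail older people are at higher risk of hospitalisation, residential care admission and death. Frailty score is the primary outcome, so the second condition plausibly selects on the outcome itself. Participants know their allocation, and the arms make quite different demands on them, so the reasons for leaving need not be the same in each arm.

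At stake is the reading of the supplement. A difference between it and the intention-to-treat result would be taken as an effect of attendance, when part of it may come from who remained at 24 months. The rule covers outcomes generally, so it reaches falls as well, where it would discard usable person-time.

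**Working it through.** The plan gives no figure for the per-protocol set, so there is none to reproduce. The check has two parts: what the condition removes, and how far it can move the effect.

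**1. What it removes.** Using the plan's attrition among all enrolled: 600 × 0.20 = 120 lost, and 600 − 120 = 480 remaining at 24 months. Completeness alone could therefore remove about 120 people before attendance is considered.

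**2. Whether the models need it.** A repeated-measures model and GEE both accept participants with some visits missing. A fall rate per person-year and time to first fall accept partial follow-up. None of them requires completeness to 24 months.

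**3. Spread of the frailty score.** No SD is stated. Inverting the sample-size statement (126 per group, difference 0.43, 90% power, two-sided 5%):

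SD = 0.43 / [(1.960 + 1.282) × √(2/126)] = 0.43 / (3.242 × 0.126) = about 1.05.

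This treats 126 against 126 as the powered comparison. If the factorial margins (252 against 252) were meant, the same formula gives 1.49.

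**4. Effect on the completer estimate.** Simulation, with these assumptions:
- normal scores at five time points, SD 1.05, lag-1 correlation 0.75 to 0.85;
- true difference building to 0.43 at 24 months;
- 20% cumulative dropout in each arm;
- in one arm, log-odds of leaving rising by 0.5 to 1.5 per SD of the last observed score; in the other arm, no such relation;
- difference at 24 months among completers, adjusted for baseline score.

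| Frailer people leave more often in | Completer difference (true 0.43) | Shift |
|---|---|---|
| control only | 0.34 to 0.40 | 0.03 to 0.09 towards no effect |
| intervention only | 0.46 to 0.52 | 0.03 to 0.09 away from no effect |
| both arms alike | 0.43 | about nil |

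Relative size: 0.03/0.43 = 7%; 0.09/0.43 = 21%, or about 20% before rounding. Without baseline adjustment the shift is larger. A likelihood analysis of all available visits returned about 0.43 in each case, as it should, because dropout here depends only on observed scores.

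**5. A harsher mechanism.** Suppose dropout in one arm depends instead on the unseen 24-month score, at log-odds 0.7 to 1.0 per criterion. Completers then give 0.24 to 0.29 (control arm) or 0.57 to 0.62 (intervention arm). That is a shift of 33% (0.14/0.43) to 44% (0.19/0.43). With the same relation in both arms (0.7) the estimate is 0.44. This is missing-not-at-random, so using all available visits would not be expected to remove the bias.

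**The case against.** **The analysis is supplementary.** Intention-to-treat is primary, joint modelling of missing data is planned as a sensitivity analysis for the primary outcome, and no sample size rests on the per-protocol set. This stands and is why the point is minor. A reader might infer that the trial's main result is biased. The text does not support that, because the primary set keeps everyone randomised.

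**The bias needs dropout that differs by arm.** This stands too. Nothing in the article shows such a pattern, and the control arm is itself an attended weekly group. The article makes it possible, not likely.

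**Larger figures are tempting.** Biases of 21 to 37% follow if the score is given an SD of 2.5. But a count of five criteria with mean 1.68 cannot have an SD above √(1.68 × 3.32) = 2.36, and the plan's own figures imply about 1.05. The 33 to 44% in step 5 rests on dropout driven by a score nobody observed, and the article gives no ground for assuming that. A reader might also infer that 20% of attenders would be dropped. The 20% is for all enrolled, and attenders may leave less often.

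**The wording may be looser than it looks.** Observed cases could simply mean no imputation, and the text does not say whether a missed intermediate visit excludes someone. It therefore cannot be read as requiring every visit. Even so, the parenthesis defines the term by measurement through to 24 months, and if something else was meant it still needs correcting.

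**An attendance-only set is also selected after randomisation,** and a model that assumes missing-at-random projects scores beyond death. Both are true. A comparison of 24-month survivors is a fair descriptive display; it should just not carry the per-protocol label.

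**Conclusion.** The concern holds as a minor point. The per-protocol set combines programme participation with being measured to 24 months, and the second condition selects on survival and retention and drops valid earlier data. The resulting effect can be biased in either direction if outcome-related dropout differs by arm: roughly 7 to 20%, or 0.03 to 0.09 of a criterion, and close to nil if it does not.

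The size rests on assumptions the article does not settle: an SD of 1.05, approximate normality of a 0-to-5 count, 20% dropout in each arm, the correlations and dropout slopes above, baseline adjustment, and dropout dependence confined to one arm. With the slope fixed per SD, the shift scales with the SD. At 1.49 it would be 0.03 × 1.49/1.05 = 0.04 to 0.09 × 1.49/1.05 = 0.13. The intention-to-treat primary result is untouched.

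**What to change.** - Define the per-protocol set by programme participation alone.
- Analyse all available visits of those participants in the planned repeated-measures model, and all their recorded person-time for falls.
- If a 24-month completer comparison is wanted, report it separately and label it descriptive.

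The cost is a change of wording; no new data or visits are needed. There are two downsides to state in the plan. The analysis then relies on missing-at-random after withdrawal or death. An attendance-defined set is still selected after randomisation, so it remains supportive only.
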